| Primary Objective | To demonstrate that PP in spontaneously breathing patients decreases the risk of acquiring the following events, which can be seen as a composite endpoint:  - Endotracheal intubation  - Or non-invasive ventilation at 2 pressure levels  - Or death |
| Secondary objectives | To demonstrate that the use of PP improves (decreases) the World Health Organization (WHO) ordinal scale score by 2 points from randomization (CAO; N Engl J Med; 2020)  To demonstrate that PP in spontaneously breathing patients reduces the need for tracheal intubation and invasive mechanical ventilation.  To demonstrate that PP in spontaneously breathing patients reduces the use of non-invasive ventilation at 2 pressure levels.  To demonstrate that PP in spontaneously breathing patients reduces the time on oxygen therapy.  To demonstrate that PP reduces the length of hospital stay  To demonstrate that PP in spontaneously breathing patients decreases mortality at day 28 in COVID-19 patients.  To compare the in-hospital mortality of the 2 groups (PP and usual care)  To compare the incidence of the need for transfer to ICU between the 2 groups  To compare the incidence of the use of non-invasive ventilation and intubation between the 2 groups, over the entire hospital stay when the stay is longer than 28 days. |
| Primary Endpoint | The rate of treatment failure defined as a composite endpoint comprising intubation and/or non-invasive ventilation at 2 pressure levels and/or death, in each group. |
| Secondary Endpoints | The duration (in days) to improve (score decrease) the clinical WHO ordinal scale score from randomization to 28 days between the 2 groups  The rate of endotracheal intubation (%) for invasive mechanical ventilation at 28 days between the 2 groups  The rate of non-invasive ventilation at 2 pressure levels at 28 days between the 2 groups  The time on oxygen therapy from inclusion to day 28 between the 2 groups  The hospital length of stay between the 2 groups  The mortality at 28 days and during the hospital stay between the 2 groups  The rate of transfer to ICU at 28 days  The rate of use of non-invasive ventilation at 2 pressure levels and intubation over the entire hospital stay. |

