# Objectives of the study

## Primary objective

To demonstrate that PP in spontaneously breathing patients decreases the risk of acquiring the following events, which can be seen as a composite endpoint:

- Endotracheal intubation

- Or non-invasive ventilation at two pressure levels

- Or death

However, we plan to include only patients without an order to not intubate so that if an imminent life-threatening respiratory occurs, intubation will be performed. Thus, only sudden unexpected death not likely to be related to respiratory function could occur and be counted in this composite criterion without endotracheal intubation or non-invasive ventilation.

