## Secondary endpoints

The duration (in days) to improve the clinical WHO ordinal scale from randomization to 28 days between the 2 groups (PP and usual care). This scale is recommended by the WHO (<http://www.who.int/blueprint/priority-diseases/key-action/novel-coronavirus/en/>) and was used in clinical trial of COVID-19 (CAO; N Engl J Med; 2020). This scale is relevant but it could be difficult to use for overloaded wards during an epidemic to exhaustively survey all points. Moreover, because the unit of time is the day, the score is imprecise (e.g., for reasons of feasibility, it is not possible to envisage twice-daily surveying). For this reason, the scientific committee chose not to use this endpoint as primary endpoint.

The rate of endotracheal intubation (%) for invasive mechanical ventilation at 28 days between the 2 groups

The rate of non-invasive ventilation at two pressure levels at 28 days between the 2 groups

The time passed on oxygen therapy from inclusion to day 28 between the 2 groups

The hospital length of stay between the 2 groups

The mortality at 28 days and during the hospital stay between the 2 groups

The rate of transfer to ICU at 28 days

The rate of use of non-invasive ventilation at 2 levels pressure and intubation over the entire hospital stay.

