## Emergency treatment

If PP induces a major decrease in SpO2 for more than 5 min or a non-resolving tachycardia despite a return to the classical sitting position or an adaptation of the oxygenation or non-invasive ventilation parameters by the clinician in charge of the patient, we will record this event as a non-serious AE if the supine position improves this parameter. However, if, despite the supine positioning, the patient does not show improvement of respiratory parameters, we will record a serious AE related to the PP.

If the respiratory signs deteriorate significantly, the use of non-invasive ventilation with 2 pressure levels or intubation will be possible if the clinician in charge of the patient considers it necessary. If intubation is considered unreasonable because of the evolution of the disease and vital parameters, although the patient would have initially received treatment in the ICU, appropriate care will be implemented for comfort in accordance with the practices of each department.

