## Statistical methods

A detailed analysis plan will be developed prior to the start of the study. The plan will be modified, if necessary, before the statistician is unblinded.

Oatient characteristics will be described by randomization group as number and percentages for categorical variables and mean (standard deviation) or median (25th and 75th percentile) for continuous variables, depending on their distribution.

The main analysis will be conducted on an intention-to-treat basis. However, data for patients withdrawing their consent during the study, in accordance with French law, will not be analyzed.

The primary endpoint (percentage of patients requiring intubation or non-invasive ventilation at 2 pressure levels, or who died within 28 days of inclusion) will be compared between the 2 groups (PP and usual care) by a Mantel-Haenszel 2-test stratified on the stratification variables #2 and #3 (SpO2 and BMI). The effect of the intervention will be expressed in terms of absolute risk difference and its 95% confidence interval (CI). The result of this analysis will be confirmed by a mixed-effect logistic regression analysis, with the recruiting center as the random effect and the study intervention and the stratification variables 2 and 3 as fixed effect variables. Interaction terms between the stratification variables and the intervention will be introduced into the model and retained only if they show a significant effect on the frequency of the outcome. Logistic regression analysis will be used to estimate the odds ratio and its 95% CI.

The binary secondary endpoints (intubation rate, rate of non-invasive ventilation at 2 pressure levels, rate of transfer to ICU, mortality) will be compared between the groups using the same method.

The time to clinical improvement (decrease of 2 points on the WHO scale) will be compared between groups by log rank test and presented as Kaplan-Meier curves. The difference in risk between the groups will be expressed as a hazard ratio (HR) and its 95% CI. This analysis will be secondarily adjusted for stratification variables, and possibly other covariables that would be misbalanced between groups, using a Cox proportional model provided the proportional assumption is verified.

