The durations (of oxygen therapy, non-invasive ventilation, hospitalization), will be compared between groups by Mann-Whitney U test adjusted for stratification variables [KAWAGUCHI; Statistics in Biopharmaceutical Research; 2011]. The difference in duration (of oxygen therapy, non-invasive ventilation, hospitalization) between groups will be expressed by its median and 95% CI obtained by bootstrapping (2000 unstratified samples).

We will conduct a per-protocol analysis including only patients of the intervention group who laid in a prone position for at least 2 hr each day, and patients of the usual care group who never laid in a prone position.

The above analyses will be repeated in prespecified subgroups formed according to the stratification variables #2 and #3 (SpO2 and BMI).

No interim analysis is planned.

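### Oxygen time and hospital stay are compared as raw durations with no rule for death, so an early death counts as a favourable value: a true benefit is diluted and, mainly for oxygen time, can reverse

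*Protocol*

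**What the plan says.** Section 8.1 (Statistical methods) fixes both the test and the effect measure for the durations. The test: "The durations (of oxygen therapy, non-invasive ventilation, hospitalization), will be compared between groups by Mann-Whitney U test adjusted for stratification variables". The difference "will be expressed by its median and 95% CI obtained by bootstrapping (2000 unstratified samples").

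The Secondary endpoints section defines the two listed durations briefly: "The time passed on oxygen therapy from inclusion to day 28 between the 2 groups" and "The hospital length of stay between the 2 groups". Neither definition says what value a patient who dies receives, and the first does not say whether days on a ventilator are days on oxygen.

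The synopsis gives the direction: "To demonstrate that PP in spontaneously breathing patients reduces the time on oxygen therapy". It words the hospital-stay objective the same way.

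Three other places bear on the reading:
- Section 5.4 (Research duration) counts hospitalization over all wards together, so a move to intensive care does not end the stay.
- The schedule under Patient follow-up (section 5.3) ends treatment at discharge or at intensive care with mechanical ventilation.
- Section 8.5 expects no missing endpoint data. That does not deal with a duration cut short by death.

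The duration of non-invasive ventilation appears in section 8.1 but is not a listed endpoint in the synopsis or in the Secondary endpoints section.

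**The concern.** A rank test on raw durations treats every short value alike. A patient who dies on day 3 has a 3-day stay and at most 3 days of oxygen, and so ranks with the patients who recovered fastest. If prone positioning prevents deaths, it replaces these short values with longer ones. Part of the benefit is then lost or, in the worst case, reads as harm.

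The two endpoints differ in what cuts them short. For stay it is death alone. For oxygen time it is death and, if ventilated days are not counted, also every intubation or switch to non-invasive ventilation. In that case the secondary endpoint is shortened by the very event that the primary endpoint counts as failure.

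At stake is the reading of two secondary objectives that the protocol sets out to demonstrate.

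**Working it through.** **1. The plan's own figure.** Section 8.2 gives 268 patients for 14% vs 4% or 24% vs 10%, with two-sided 5% and at least 80% power. Use n per arm = [1.96·√(2·p̄·q̄) + 0.8416·√(p₁q₁ + p₂q₂)]² / (p₁ − p₂)².
- 14% vs 4%: (1.96·√0.1638 + 0.8416·√0.1588)² / 0.01 = 127.4, so 128 per arm, 256 in total, and 262 after dividing by 0.98 for losses. Power at 134 per arm is 82.0%.
- 24% vs 10%: (1.96·√0.2822 + 0.8416·√0.2724)² / 0.0196 = 111.8, so 112 per arm, 224 in total. Power at 134 per arm is 86.7%.

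So 268 is consistent with the plan. It gives the failure rates used below. The protocol states no figure for the durations.

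**2. Limiting case for the rank test.** Let θ = P(prone duration longer than control) + half of ties, so θ above 0.5 makes prone look worse. Let f_C and f_P be the proportions whose duration is cut short. Suppose every such value is shorter than all the others and the arms are otherwise identical. Then

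θ = (1 − f_P)·f_C + ½·[(1 − f_P)(1 − f_C) + f_P·f_C] = 0.5 + 0.5·(f_C − f_P).

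At 24% vs 10%: 0.216 + ½·(0.684 + 0.024) = 0.570. At 14% vs 4%: 0.550. If the same patients are ranked worst, the sign changes: 0.430 and 0.450.

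**3. Oxygen time if it stops at failure.** Simulation with 134 per arm, 1000 trials per scenario and an unstratified Mann-Whitney test. Assumptions that the protocol does not give: non-failing patients lognormal with median 7 days and log-SD 0.7, capped at 28 and equal in both arms; failure times lognormal with log-SD 0.6.

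| Median day of failure | θ, 24% vs 10% | Significant against prone | θ, 14% vs 4% | Significant against prone |
|---|---|---|---|---|
| 1 | 0.568 | 48% | 0.549 | 29% |
| 2 | 0.558 | 38% | 0.542 | 23% |
| 4 | 0.532 | 16% | 0.521 | 8% |
| 7 | 0.501 | 2% | 0.500 | 3% |
| 12 | 0.469 | 0% | 0.479 | 0% |

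If prone also shortens recovery by 10% in non-failing patients, θ at 24% vs 10% falls to 0.539, 0.523, 0.493, 0.463 and 0.432. Reversal therefore needs failures that come before typical recovery.

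**4. Hospital stay, all wards, cut only by death.** Assumptions: non-failing median 8 days; ventilated survivors 15 or 20 days; 30% or 50% of failures fatal; death at median day 3, 6, 10 or 14; 800 trials per scenario.
- 24% vs 10%: θ from 0.453 to 0.505, significant against prone in 0–3%.
- 14% vs 4%: θ from 0.467 to 0.503, significant against prone in 0.1–4%.
- Mean θ passed 0.50 only with death at median day 3 and half of failures fatal, and by at most 0.005.

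**5. Loss of benefit.** At 24% vs 10%, with ventilated days counted and stay taken over all wards, the raw test is significant for prone in about 3–20% of trials. Days alive and free give about 32–39%. The gain depends on how long ventilated survivors are assumed to stay, and it is smaller if they leave sooner.

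**6. Duration of non-invasive ventilation.** If never-ventilated patients enter as 0, at most 24% of an arm can have a value above 0 at the planned rates. Both medians are then 0. The share of between-arm pairs that are 0 against 0 is 0.76 × 0.90 = 68%, so the median pairwise difference is also 0, and a bootstrap interval comes out as [0, 0].

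**The case against.** The strongest reply is that hospital stay is largely protected. It runs over all wards, so ventilated survivors have long stays, and these count against the arm with more failures. This stands. A reader might infer that intubation shortens the stay, or that the analyses will tend to show prone positioning prolonging both durations. The documents do not support either: step 4 shows dilution, with reversal only at the edge of the range.

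For oxygen time, the protocol does not say that counting stops at ventilation. The endpoint runs to day 28, and only the schedule hints at an earlier end. The reversal in step 3 is therefore conditional on both the definition and the timing. This also stands.

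A reader might take the roughly 50% of trials that favour prone when all failures are ranked worst as the gain from the fix. It is not, because the fix scores only deaths as worst. The relevant comparison is step 5.

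It can also be said that unventilated deaths should be few. Do-not-intubate orders are excluded, and the Primary objective section holds that "only sudden unexpected death not likely to be related to respiratory function could occur" without ventilation. Section 6.3 provides for another case: "If intubation is considered unreasonable because of the evolution of the disease and vital parameters". The two passages should be reconciled, but they do not show that early deaths will be common. Nor do they make the separate intubation and ventilation rates wrong, since mortality is reported beside them and the primary composite includes death.

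Finally, the statistical analysis plan, which is not shown, may hold a rule for death. That is possible, but the protocol already fixes the variable, the test and the effect measure. Taken as written, they score an early death as a good result.

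**Conclusion.** The point holds in a limited form. Section 8.1 compares oxygen time and hospital stay as raw durations with no rule for death, so early deaths enter as favourable values.

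- **Stay:** the consequence is dilution of a true benefit. Reversal is possible only if deaths are early and make up a large share of failures.
- **Oxygen time:** the consequence depends on a definition that the protocol leaves open. If ventilated days are not counted, the result can reverse when failures precede typical recovery, and the reversal is gone at a failure median of about 7 days, the assumed recovery median. If they are counted, the consequence is again dilution.
- **Non-invasive ventilation duration:** the planned median difference carries no information if never-ventilated patients enter as 0. Section 8.1 does not say whether they do.

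All simulated percentages rest on assumed distributions and an unstratified test, so the pattern across the range matters more than any single figure. These are secondary endpoints; the primary analysis and the sample size of 268 are not affected.

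**What to change.** In section 8.1 and the Secondary endpoints section, replace the two durations by days alive and free of oxygen to day 28 and days alive and out of hospital to day 28. Score deaths by day 28 as 0, and state that ventilated days count as oxygen days. Keep the same stratified Mann-Whitney test.

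Ranking deaths worst within that test is an alternative. The two are not identical: a score of 0 ties a death with a patient still on oxygen or in hospital at day 28, while a worst rank places the death below. Choose one and state it.

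Drop the duration of non-invasive ventilation, which is not a listed endpoint, or replace it by ventilation-free days with death scored 0.

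The cost is rewording. The data and the test stay the same, and section 8.5 already provides for vital status at day 28 after discharge. The one downside is that a composite of days is slightly less direct to read than a raw duration.

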| Study Method/ Design | This will be 2 parallel-group randomized controlled trial with 1:1 allocation ratio to usual care or intervention (PP).  The control group will be usual care in all participating departments/hospitals. The prone position will not be allowed during the day (allowed at night if it is the patient’s natural sleeping position).  The intervention group will undergo the following:   - Each day of hospitalization, at least 2 PP sessions during the day, with the objective to spend as much time as possible in PP if tolerated and a minimum of 2.5 hr cumulative time in PP during the day. - A session of PP as long as possible at night. Patients will be encouraged to sleep in PP as much as possible at night, knowing that monitoring the number of hours will not be feasible in COVID-19 medical wards in the current context.   Bedridden patients who are not able to self-position to the prone position or with minimal assistance of one person will not be included in the study.  Barriers will be positioned to avoid a potential fall out of bed.  The patient will be allowed to choose the best PP as long as the back of the thorax is not compressed by the bed. |
| Inclusion criteria | Patients > 18 and < 85 years old  Patients hospitalized with a laboratory-confirmed SARS-CoV-2 infection  Patients on oxygen therapy (nasal cannula, mask or high-flow nasal oxygen therapy)  Patients able to self-position to the prone position or with minimal assistance of one person  Signed the consent form  Patients hospitalized in a COVID-19 medical ward for < 72 hr |

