## Primary endpoint

The rate of treatment failure defined as a composite endpoint comprising intubation and/or non-invasive ventilation at 2 pressure levels and/or death, in each group (PP and usual care).

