## Number of participants to be included in the research

With a rate of lost to follow-up of < 2%, a population of 268 patients would guarantee a power of at least 80% to demonstrate at the 2-sided alpha risk of 5%, a difference of 10% to 14% between the 2 groups concerning the composite primary endpoint (4% vs 14% or 10% vs 24%). The number of patients to be recruited is fixed at 268.

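### Section 8.1 summarises non-invasive ventilation duration by a median difference with bootstrap CI, which at the planning rates would almost certainly be 0 (0 to 0) whatever the effect (minor)

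*Protocol*

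**What the plan says.** Section 8.1 (Statistical methods) handles durations in two sentences, and NIV is named in both. The first sets a Mann-Whitney test adjusted for the stratification variables. The second sets the effect measure: "The difference in duration (of oxygen therapy, non-invasive ventilation, hospitalization) between groups will be expressed by its median and 95% CI obtained by bootstrapping", with 2000 unstratified samples. The main analysis is by intention to treat, and no separate population is given for durations. The same section repeats its analyses in the SpO2 and BMI subgroups.

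Three other places bear on how many patients can have an NIV duration:

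- The primary endpoint is a "composite endpoint comprising intubation and/or non-invasive ventilation at 2 pressure levels and/or death, in each group", and section 8.1 gives its window: "percentage of patients requiring intubation or non-invasive ventilation at 2 pressure levels, or who died within 28 days of inclusion".
- Section 8.2 gives the planned rates, "concerning the composite primary endpoint (4% vs 14% or 10% vs 24" per cent, and states that "The number of patients to be recruited is fixed at 268".
- The non-inclusion criteria rule out patients with an indication for curative NIV, so nobody should enter the trial needing it.

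The listed NIV endpoint is a rate: "The rate of non-invasive ventilation at two pressure levels at 28 days between the 2 groups". The synopsis and the sections on secondary objectives and secondary endpoints list NIV rates (to day 28 and over the whole hospital stay). NIV duration is in none of these lists; it appears only in section 8.1.

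**The concern.** A median describes a duration that most patients have. Every patient enters on oxygen and in hospital, so the rule suits two of the three durations. For NIV, the plan's own rates imply that most patients in each arm have none. If they count as 0 days, both arm medians sit at zero and a bootstrap reproduces that zero. The line in the report would carry no information about the intervention, although a zero-width interval looks like a precise result. If they are left out, the arms are compared on a subset that the intervention is itself meant to change, so randomisation no longer protects the comparison. The protocol does not say which applies, and neither gives a usable between-group estimate.

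**Working it through.** **Inputs.** Planned composite rates 4% vs 14% or 10% vs 24%, and N = 268 (section 8.2); "2 parallel-group randomized controlled trial with 1:1 allocation ratio" (synopsis), hence 268 / 2 = 134 per arm; 28-day window and 2000 resamples (section 8.1). I take the lower rate to be the prone arm, as the hypothesis implies.

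**1. Reproduce the plan's figure.** Section 8.2 claims "a power of at least 80% to demonstrate at the 2-sided alpha risk of 5"%. With the pooled-variance formula without continuity correction,

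n per arm = [1.96 √(2p̄(1−p̄)) + 0.8416 √(p₁(1−p₁)+p₂(1−p₂))]² / (p₁−p₂)²

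- 4% vs 14%, p̄ = 0.09: (0.793 + 0.335)² / 0.01, about 127.4, so 128 per arm and 256 in total; 256 / 0.98 gives 262. Power at 134 per arm is 82.0%.
- 10% vs 24%, p̄ = 0.17: (1.041 + 0.439)² / 0.0196, about 111.8, so 112 per arm and 224 in total; 224 / 0.98 gives 229. Power at 134 per arm is 86.7%.

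The 268 is consistent with these rates, so they can be taken as the plan's working assumptions.

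**2. Bound the share with any NIV.** Bilevel NIV is one component, so its 28-day rate cannot exceed the composite rate.

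| Scenario | Arm | No bilevel NIV, at least | Ventilated, at most |
|---|---|---|---|
| 10% vs 24% | usual care | 1 − 0.24 = 76% | 134 × 0.24 = 32 |
| 10% vs 24% | prone | 1 − 0.10 = 90% | 134 × 0.10 = 13 |
| 4% vs 14% | usual care | 1 − 0.14 = 86% | 134 × 0.14 = 19 |
| 4% vs 14% | prone | 1 − 0.04 = 96% | 134 × 0.04 = 5 |

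**3. Median over all randomised patients.** With 134 patients, an arm's median exceeds 0 only if 67 or more have NIV. At a 24% rate the binomial probability of that is 6.7 × 10⁻¹¹. Bootstrap samples redraw from the same mostly-zero data, so their medians are also 0.

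If the median of all pairwise differences is meant instead, the share of pairs with both members at 0 is at least 0.76 × 0.90 = 68% (0.86 × 0.96 = 83% in the other scenario). Both exceed half, so that median is 0 too.

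**4. Simulation.** NIV rates were set to the full composite rates, with 2000 resamples per trial. Duration among users was assumed uniform on 1 to 14 days; this choice does not matter while users stay well below half of each arm. The difference of medians and its CI were 0 (0 to 0) in 100 of 100 trials in both scenarios. The pairwise version gave a CI of 0 to 0 in all 10 trials per scenario (300 resamples each).

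**5. Where it stops holding.** Share of 100 simulated trials giving 0 (0 to 0):

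| NIV rate, prone vs usual care | Per arm | Share |
|---|---|---|
| 10% vs 30% | 134 | 99% |
| 20% vs 35% | 134 | 93% |
| 25% vs 40% | 134 | 60% |
| 35% vs 45% | 134 | 19% |
| 10% vs 24% | 67 | 98% |
| 10% vs 24% | 34 | 93% |
| 10% vs 24% | 20 | 63% |

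**6. Ventilated patients only.** From step 2, the comparison rests on at most about 13 vs 32, or 5 vs 19, patients. The bound treats every composite event as NIV, so real numbers would probably be smaller.

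**The case against.** **It is not an endpoint.** NIV duration sits in two parentheses in section 8.1. The listed NIV question, the day-28 rate, is analysed by the primary endpoint's method, with a risk difference and CI. This stands and is why the point is minor.

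**The analysis plan may say who counts.** Whether unventilated patients score 0 or are left out is a detail a protocol may leave to the statistical analysis plan, and section 8.1 announces one. This stands for the choice of population. It does not rescue the estimator, which the protocol itself names: one choice gives an empty result, the other a post-randomisation comparison.

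**The zero would not stand alone.** The Mann-Whitney test remains valid with many ties at zero, and the methods paper cited for it concerns, by its title, stratified Mann-Whitney estimators, so another effect measure may be available. This also stands; the fault lies in the median and its interval.

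Three stronger readings go further than the documents allow:

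- That the result is always 0 (0 to 0). It is near certain only around the planning rates and in groups that are large enough. Moreover, the 76% bound covers bilevel NIV to day 28, whereas the duration sentences state neither limit. Single-level support or later use is not strictly bounded.
- That a significant test would usually sit beside the zero interval. How often depends on what share of composite events are NIV, and the protocol gives no split.
- That a ventilated-only comparison would make prone positioning look harmful. The direction and size depend on which cases are prevented and how duration rises with severity; the protocol fixes neither. What the documents support is that the subset is small and selected after randomisation.

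**Conclusion.** Wrong as written, and minor. At the section 8.2 rates, the planned median difference in NIV duration over all randomised patients would almost certainly be 0 days (95% CI 0 to 0) regardless of the effect, under either reading of the median. This rests on three assumptions: composite rates close to plan, patients without NIV counted as 0 days, and NIV meaning bilevel NIV within 28 days. It is no longer dependable when an arm's rate approaches 35-40%, or in subgroups of about 20 per arm. The alternative population does not repair it. The primary analysis, the sample size, oxygen time, hospital stay and the NIV rate are unaffected.

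**What to change.** Delete non-invasive ventilation from both duration sentences in section 8.1. Keep the day-28 NIV rate, with its risk difference and CI, as the between-group NIV comparison. Describe NIV duration among ventilated patients by arm, without a test or a between-group interval.

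The cost is one wording change. It needs no new data and loses no listed endpoint, and section 8.1 allows the analysis plan to be modified before the statistician is unblinded. What is given up is a formal comparison of NIV burden.

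Mean NIV days over all randomised patients should not be substituted as it stands. Patients who die or are intubated early accrue few NIV days, so worse outcomes could look better. Such a measure would first have to account for death and intubation.
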